## Abstract

**Background:**

Workplace Health Promotion Programs (WHPP) have been shown to be an efficient way of improving workers’ health. These programs can be incorporated in the worker’s daily schedule and improve their productivity at work. Improving employees’ health also benefits the employers by increasing their return on investment and lowering healthcare costs. The *Activate Your Health* program, created by Capsana in 2015, is a WHPP targeting multiple lifestyle habits for a three-year period. This WHPP includes tailored web-based interventions and the support of different health professionals throughout the years. We hypothesize that this approach will yield long-term lifestyle changes. The objective of the current paper is to describe the *Activate Your Health* program’s design.

**Methods/design:**

Eleven companies are taking part in this WHPP and had to choose among five different options of this program and all their employees were encouraged to participate. Each option differs by the number and type of interventions included. The limited option, which is considered the control group, only consists in completing a questionnaire regarding their health status, lifestyle habits and behaviors. On the other end, the extensive option receives a combination of multiple interventions: online menus, health challenges, support in creating a healthy work environment, coaching by health professionals (nurse, nutritionist, and kinesiologist), health screening and flexibility assessment, online resources, social health platform, and activity tracking. The remaining options are in between these options and vary by the amount of intervention. Baseline data are already gathered; two other data collection periods will take place after one and 2 years into the program. The primary outcomes of the current program are physical activity and fitness measures, nutritional data, smoking habits, stress and intention to change.

**Discussion:**

The *Activate Your Health* program will allow us to compare which combinations of interventions are the most effective. It is expected that the extensive option will be the most advantageous to improve lifestyle habits. The results will indicate the strength and weakness of each intervention and how it could be improved.

**Trial registration:**

Clinicaltrails.gov, registration number: NCT02933385 (updated on the 26th of March 2019, initially registered on the 5th of October 2016).

## Background

The World Health Organization states that chronic conditions are the leading cause of death and disability worldwide [1]. More than one out of every five Canadian lives with one of the following chronic conditions: cardiovascular disease, cancer, chronic respiratory disease, or diabetes [2]. These four chronic diseases represent 67% of annual deaths [3].

In Canada, 50% of workers live with a minimum of one chronic condition [4]. This situation increases absence rates due to functional limitations and creates a financial burden to the employers [5]. Moreover, poor health and unhealthy lifestyle habits were observed to decrease productivity [6]. Thus, decreasing chronic conditions is crucial. This could be achieved by adopting healthy lifestyle habits [7, 8]: i.e., being physically active, eating healthy, limiting alcohol and tobacco, and having good sleep habits, [9] which can prevent at least 70% of major chronic diseases [10]. Engaging in 180 min of moderate intensity physical activity (PA) per week, which is roughly the recommended amount of PA, decreases the risk of mortality [11]. However, it has been noted that the Canadians lack compliance to the recommendations for a healthy lifestyle. For example, 78% of Canadians are not sufficiently active and 60% have poor eating habits [12]. It is also encouraging to note that partly fulfilling the recommendations could have beneficial effects on health. For example, a sedentary individual who does any PA would benefit from a decrease in mortality risk [11].

Some of the reasons for failing to comply with these healthy lifestyle recommendations are a lack of time, social norms, built environment and cost [13]. As workers spend roughly 8 h per day at work [14], a program targeting changes in the lifestyle habits could begin at the workplace. To do so, some companies have started seeking the help of health specialists to improve their workers’ lifestyle habits and working environment by implementing a workplace health promotion program (WHPP). Studies indicate that these programs are beneficial for the workers’ physical [15, 16] and mental [17, 18] health, but also improve their work performance by increasing productivity [19, 20] and decreasing absenteeism [21]. These changes indirectly reduce health-care costs [22] and increase “return on investment (ROI)” [19, 22]. Hence, WHPP would advantage the workers, employers and the society as a whole [23–25]. However, this type of program needs to be designed properly. For example, a WHPP offering only a health-related questionnaire and/or an online platform does not lead to a successful outcome [26]. Moreover, to detect the population health effects and to yield a positive ROI, a minimum of 3 years of implementation is suggested [26].

Capsana is a Canadian organization dedicated to promoting healthy lifestyle habits, and preventing and managing chronic diseases in the workplace for the past 25 years. In 2015, Capsana [27] created a program called “*Activate Your Health*”. This WHPP allows workers to adopt healthy lifestyle habits in their workplace with web-based and tailored interventions along with personalized advice over a 3-year period. The program also helps workers identify their risk factors associated with chronic diseases. In addition, it also assists the employers in changing the culture of health within the company in the goal of supporting the employees in achieving a better health profile and lifestyle habits. The eventual goals of the evaluation component of the *Activate Your Health* program are to evaluate the effectiveness of this WHPP on the short and long term, investigate which workers would benefit the most, compare the responses to the different interventions, and identify the challenges associated with the implementation of this type of program in the participating workplaces. We hypothesize that the option targeting several lifestyle habits at once will yield the biggest improvement in health and work-related parameters. The aim of the current paper is to describe the *Activate Your Health* WHPP.

## Methods/design

### Study design

The *Activate Your Health* program is an already-existing three-year program that was designed and implemented by Capsana in Canada (Quebec). This quasi-experimental study with an exploratory framework takes into account previously identified limitations regarding WHPP and interventions that previously have been shown to be beneficial [26, 28, 29]. The baseline data was collected between December 2016 and July 2018. The employees will be re-evaluated one and 2 years into the program. There was no specific risk associated with participating in this program other than the ones associated with the adoption of an active lifestyle. The Health Research’s Ethic Committee of Université de Montréal approved this study (16–063-CERES-D (1)). The study was registered on Clinicaltrials.gov on 16th of October 2016, and was updated on the 26th of March 2019 (NCT02933385).

All the gathered information was kept confidential and was not shared with any employers. The employers received only an overall report regarding the health of their employees without any given individual’s portrait. Participating employees were aware of this and also knew that the data collected throughout the *Activate Your Health* WHPP would be part of a research study. Only certain Capsana’s employees associated with data management and the research team had access to this information.

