Employees are offered assistance in maintaining or improving their lifestyle habits. They have the opportunity to talk, through the phone or in person, to a nurse and receive personal motivational coaching to enhance, among others, psychological health, well-being and lifestyle habits, and to reduce stress (Year 1). The following years, they will have the opportunity to talk to a nutritionist (Year 2), and to an exercise specialist/kinesiologist (Year 3).

#### Closing events – year 1, 2, and 3

At the end of each year, at the work site, employees will take part in a closing event organized by Capsana. An example of this is “Jeux Spin [31]” which consisted of various recreational activities such as soccer in an inflatable structure. It is to note that for logistic reasons, these events are offered to the participating companies (not just the participants of the *Activate Your Health* program). These events aim to congratulate the employees for taking control over their own health and motivate them to maintain their acquired/improved habits.

#### Health screening and flexibility assessment – year 1, 2, and 3

A team of nurses meets the employees individually to screen for their risk factors. The goal of this intervention is to identify any abnormal blood profile (unfasten state). It serves as an indicator and does not replace a regular blood test. If any abnormal results were found, employees were encouraged to consult their family doctor in order to do a follow-up. The plasma HDL level and HDL/total cholesterol ratio (CardioChek P.A.®-LIT001539, QC, Canada) and glucose concentration (Contour®Next - 85,303,759, New Jersey, US) are measured. Blood pressure is manually taken using the conventional auscultatory method (stethoscope: 3 M™ Littmann® Classic II S.E-MMM2201, US; sphygmomanometer: Welch Allyn & Tycos model, Boston, US). Employees are asked to stand erect in order to take their height using a vertical stadiometer (Seca213, Hamburg, Germany), and weighed using a scale (Tanita-BF-350, IL, US). Waist circumference is measured at the iliac crests using a measuring tape. The “sit-and-reach” test (Sit and Reach Test Tester- EN-121085, NY, US) is performed to determine posterior chain flexibility. The results of these tests are available to the employees at the end of their session, and the nurse gave appropriate health advice to improve their health profile.

#### CANRISK questionnaire – year 1, 2, and 3

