One of the advantages of the *Activate Your Health* program is the varying number of interventions, which allows us to compare the effect of different combinations of interventions on health and work-related variables. We did exclude the option D as none of the companies chose that option. We can deduct that such an option might be less appealing for companies. It would have been interesting to compare the option A, which contains all the interventions targeting eating and PA habits vs. the option D, which had only interventions improving eating habits. Nevertheless, we do have the limited option (control group) that did not receive any interventions to compare the effectiveness with the other options. Moreover, Nöhammer et al. (2010) suggested that WHPP could benefit from documenting the employee’s perspective of the interventions. At the end of the current WHPP, a questionnaire regarding each intervention will be sent to all the employees, in order to study their perspective. Also, throughout the year, Capsana also supports each company in the creation of a favorable environment by providing advice and/or help [46]. Modifying the work environment by decreasing unhealthy food available at the work site within the company, for example, could have positive impact on the employees’ health and the organization as a whole [46].

Some limitations should be considered. The data collection method consists of filling questionnaires. Most of the variables of interest, such as PA level and eating habits, in the current program and its variations come from these self-reported answers. Objective measures such as accelerometer data could have been used to identify the changes that are taking place within the different options. Moreover, participants who have successfully changed their lifestyle habits will be more inclined to remain actively involved in the *Activate Your Health* program, and to be reassessed, which was the case in another study [47]. In addition, Nilsen et al. [47] (2014) noted the majority of their participants with diabetes who dropped out were the participants with a poor life satisfaction and needed help with their lifestyle habits. Taking these observations into account, specific analysis will be performed to examine this aspect in *Activate Your Health*.

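### Listed outcomes are last measured 2 years into a 3-year programme, so the planned data cannot evaluate year-3 delivery, including the kinesiologist coaching

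*Protocol article*

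**What the plan says.** The Study design section of the protocol article describes the intervention this way: "program is an already-existing three-year program that was designed and implemented by Capsana". The same section gives the assessment times: "The employees will be re-evaluated one and 2 years into the program". The abstract agrees, stating that baseline is complete and that "two other data collection periods will take place after one and 2 years into the program". The Statistical analyses section builds its mixed models and GEE on the 1-year and 2-year measurements.

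The coaching subsection of the intervention description assigns a nurse to year 1 and then says: "The following years, they will have the opportunity to talk to a nutritionist (Year 2), and to an exercise specialist/kinesiologist (Year 3". Table 1 places coaching in options A, B and C, which are all the intervention options that any company chose.

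The aims are wider than this schedule. The abstract states: "We hypothesize that this approach will yield long-term lifestyle changes". The end of the Background sets out to evaluate effectiveness in both the short and the long term and to compare responses to the different interventions. The Discussion expects better adherence and effectiveness in options A, B and C because a nurse, a nutritionist and a kinesiologist give support over the three years. It closes with the goal of saying which type of intervention works best and for whom.

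**The concern.** An intervention can be evaluated only on outcomes measured after it has been delivered. Here the professional support is sequenced by year, and the last professional to join has not started when the outcomes are measured for the last time. Physical activity is listed first among the primary outcomes, and coaching by an exercise specialist bears on it directly.

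Two misreadings could follow. A small or null 2-year change in physical activity could be reported as a verdict on the whole programme when its exercise coaching was still to come. A favourable 2-year change could be credited to a three-year programme of which only two years had run. Neither could be corrected afterwards, because a missed final wave cannot be recovered.

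**Working it through.** No sample size or power figure bears on this point. The check sets the assessment schedule against the delivery schedule.

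**Inputs**
- Programme length: 3 years = 36 months (Study design).
- Outcome waves: baseline, 1 year and 2 years = months 0, 12 and 24 (abstract, Study design, Statistical analyses).
- Baseline window: "The baseline data was collected between December 2016 and July 2018" (Study design).
- Coaching: nurse in year 1, nutritionist in year 2, kinesiologist in year 3 (coaching subsection).

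**Alignment**

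| Programme year | Months | Coaching | Outcome wave at end of year |
|---|---|---|---|
| 1 | 0–12 | Nurse | Month 12 |
| 2 | 12–24 | Nutritionist | Month 24 |
| 3 | 24–36 | Kinesiologist | None |

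Time after the last wave: 36 − 24 = 12 months, and 12/36 = one third of the programme.

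**Calendar.** Adding 24 months to the baseline window puts the last planned wave at about December 2018 to July 2020. Adding 36 months puts the end of year 3 at about December 2019 to July 2021.

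**The article's own delivery example.** The allocation section describes an intervention given in January 2017 and repeated in January 2018 and 2019. If that company's baseline was December 2016 (an assumption, the earliest date in the window), the deliveries fall at months 1, 13 and 25. The third comes after the month-24 wave.

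**Does the questionnaire's label imply a later wave?** The Data collection tools section labels the questionnaire for years 1, 2 and 3. The abstract counts baseline plus two further collections: 1 + 2 = 3 waves. The label therefore fits months 0, 12 and 24 and does not establish a month-36 wave. No month is stated, however. If the third wave slipped m months into year 3, the unmeasured part would be (12 − m)/36: 9/36 = 25% for m = 3, and 6/36 = 17% for m = 6. These values of m are illustrative.

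**What is collected at the end.** The allocation section provides for a yearly adherence questionnaire and an end-of-study query on adverse effects. The Discussion adds: "At the end of the current WHPP, a questionnaire regarding each intervention will be sent to all the employees". That form concerns employees' perspective. None of the three appears under the primary or secondary outcomes.

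**The case against.** The schedule is stated openly and consistently, the study is described as exploratory, and long term is never defined as 36 months. No planned test or estimate is invalid. Because options A, B and C all contain the coaching, its late start does not bias comparisons among them. All of this stands, and it is why the point concerns the scope of the conclusions and not an error of analysis.

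Three stronger readings are tempting, and the documents support none of them.

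- **That the article's own minimum duration is not met.** The Background says "a minimum of 3 years of implementation is suggested". This is about how long a programme runs, and this one runs for three years. The statement is also a suggestion, tied to population health effects and return on investment, and it is not a requirement for detecting changes in self-reported habits.
- **That physical activity is last measured before anything aimed at it is delivered.** The Health Challenge, the workplace-environment support, the conferences and the social platform run from year 1, and the activity tracker is given in year 1. A 2-year physical-activity result is informative about a programme with those components but without its exercise coaching.
- **That year 3 goes wholly unobserved.** Adherence, adverse effects and employees' views are collected. What is absent is a measurement of the listed outcomes.

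The questionnaire's label does leave some doubt about the timing of the third wave. If the authors intend a wave at month 36, the abstract, the Study design section and the Statistical analyses section all need correcting, so a change is needed on either reading.

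**Conclusion.** The point holds at moderate weight. As written, outcome measurement covers 24 of 36 months. Year-3 delivery, including all of the kinesiologist coaching, has no later measurement on any primary or secondary outcome. The planned data can answer questions about the first two programme years. They cannot support conclusions about the full three-year programme or the year-3 coaching, which the aims in the Background and the expectations in the Discussion take in.

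This rests on two assumptions: that the 2-year wave is taken at or near the end of programme year 2, as its wording indicates, and that no further outcome wave is planned beyond those the article describes.

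**What to change.** **Preferred.** Send the existing online lifestyle questionnaire once more at the end of year 3, together with the end-of-programme questionnaire already planned for all employees. Add a 36-month time point to the mixed models and GEE for the self-reported primary outcomes. The cost is one more administration of an existing form, an ethics amendment and further non-response. That non-response may be selective, since the Discussion already expects those who changed their habits to be more likely to stay. The online form would not replace the nurse-measured screening outcomes, which would still end at 2 years, and conclusions on them should say so.

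**Otherwise.** Restate the objectives and conclusions as the effect of the first two programme years, and exclude the year-3 coaching and the complete three-year programme from what the study can conclude. This costs wording only.

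**In either case.** State the month of each wave relative to each company's programme start, so that the questionnaire's label by year and the 1-year and 2-year assessment times can be read together.

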### Recruitment of participants/study population

Through phone calls and in-person meetings, Capsana contacted the different companies to participate in their *Activate Your Health* program. Eleven companies are taking part in the current project. Among the participating companies, six were related to banks, two were related to financial markets, one was a graveyard parish, one was related to workplace health safety and security, and one was a marketing firm. The participating companies encouraged their employees to take part in this WHPP and participation was on a voluntary basis. Only pregnant women could not partake in the program. After an information session about the *Activate Your Health* WHPP and motivating their willingness to participate, an email was sent out to all the employees. Those who completed the online consent form (written) were able to fill the self-administered questionnaire.

### Intended sample size explained

Based on recruitment experience for similar workplace interventions, financial support available and pilot data yielding significant benefits for the employees and their organizations with 656 participants, this program had the potential to enrol 6000 employees [30]. Therefore, *Activate Your Health* included as many employees as possible. Also, the purpose of this program is to evaluate for the first time the overall impact of the different options on a lot of health-related variables and lifestyle habits therefore the goal was to involve as many participants. The data collected for this program will thus be used for the first time to evaluate this program and will serve as a model for sample size calculation of future studies.

### Study intervention/allocation to interventions

Capsana and their sponsors are offering the interventions throughout the year and at the same time of year throughout the 3-year period (ex: a company that received an intervention in January 2017 will receive the same intervention in January 2018, 2019). Table 1 summarizes the different interventions included in each of the five options (A to E) and the number of companies enrolled in each of them. Briefly, option A had the most extended number of interventions, and involved numerous web-based and innovative tools to improve lifestyle habits. Moreover, some interventions in option A and B were tailored and personalized to the participants’ needs while participants in option E will not receive any interventions other than the informational/motivational sessions at baseline and at the end of each year (control group). There was no concomitant care or interventions that were prohibited while taking part in this program.

**Table 1 Tab1:** Details on the interventions included in each option (*n* = 11 companies)

Interventions	Options				
	Extensive				Limited
	A (*n* = 1)	B (*n* = 1)	C (*n* = 8)	D (*n* = 0)	E (Control) (*n* = 2)
Personalised online menus	X	X	X	X	
Support in creating a favourable environment	X	X	X	X	
*Health Challenge*	X	X	X	X	
Conferences	X	X	X		
Coaching	X	X	X		
Closing events	X	X	X		
Health screening and flexibility assessment	X	X			
CANRISK questionnaire	X	X			
Distribution of publications	X	X			
Social health platform	X	X			
Activity tracker	X				
*Optional: Quit to Win! Challenge*	X	X			

The companies had to choose one out of the five options offered by Capsana. Most of the companies (*n* = 8) chose option C and none picked option D. One company chose two different options (one group was placed in option A while the others in option E). One company won a promotional draw and Capsana placed it in one of the five options (Option E). In-person interventions took place at the workplace whereas the web-based ones were accessible anywhere.

Each company started the interventions at a different time point as each company differed by the administrative work necessary for the implementation of such program. Employees were unaware that other companies were participating in the *Activate Your Health* program and that the others could have a more or less beneficial option than theirs. Participants could also withdraw from the program at any given time. Participants are welcome to communicate with the research team if they have any questions/concerns during the program. Participants are also questioned at the end of the study regarding any adverse effects that took place during the study period. An employee from Capsana visited at least once a year each company to improve the adherence that will also be monitored by completing a questionnaire at the end of each year. The research team assisted annually to at least one data collection session and one of the interventions offered in this WHPP.

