### Data collection tools

#### Self-administered questionnaire – year 1, 2, and 3

All employees taking part in *Activate Your Health* are asked to fill out an online self-administered questionnaire that is based on an adaptation of existing questionnaires, lifestyle guidelines and opinion of health experts. Participants are asked to provide basic socio-demographic, anthropometric, health, medication and work information and extreme values are checked before inclusion. Lifestyle habits are also auto-reported: PA (frequency, duration and intensity), eating habits, smoking, alcohol consumption, sleeping habits, and stress level. As the *Activate Your Health* program aims to modify the employees’ lifestyle habits, their intention to improve their habits is also evaluated. Once the questionnaire is submitted to Capsana, each of them is assigned a questionnaire ID to anonymize the data. The data are kept for 7 years by the Data Monitoring Committee. The Data Monitoring Committee is led by the principal investigator ([name]) in collaboration with one member of Capsana. It supervises data collection and analyses. For any further details please contact the principal investigator. After which, a total health score is calculated on 100 points: the higher the score, the better their health (100 equals optimal health and lifestyle habits). This score and action plan are sent to the employees personally.

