One of the potential strengths of the *Activate Your Health* is that it targets multiple modifiable lifestyle habits and biometric measures associated with a decrease in the risk of cardiovascular disease and stroke [39]: eating healthy, being physically active, discontinuing smoking, and maintaining a healthy weight, blood pressure range, blood cholesterol and glycaemia. Recent studies in the field targeting at least three habits [40, 41] were observed to be effective. Therefore, it is expected that multiple lifestyle habits in one option would lead to greater health benefits for employees. Adherence rates in WHPP are generally in the low range [42] (< 50%), and web-based interventions, when tailored, were observed to be effective [43] only for a short period of time after the study period [44]. In the current study protocol, the web-based tailored interventions are accompanied with the support of different health professionals (nurse, nutritionist and exercise specialist/kinesiologist) throughout the 3-year period. Therefore, the adherence rate and effectiveness of the options A, B and C are expected to be higher. In addition, a study [45] with a similar approach, i.e., targeting six health behaviors, but differing in the study population (male participants at high risk of cardiovascular disease without a control group), the variety of interventions offered (3.5 h of health promotion class), and study duration (6 months) led to an increase in physical activity, improved stress management, diet control, blood pressure, total cholesterol and BMI, which are some of the variables that will be included in future studies. Therefore, *Activate Your Health* might lead to similar or better results as it regroups any health profile of employees, has a longer study period, provides different interventions that are web-based, and support the company in creating a favorable work environment.

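### The one described adverse-effects question comes at the end of the study, with no provision for people who withdraw, although a questionnaire is already completed every year

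*Protocol article*

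**What the plan says.** The relevant statements in the protocol article are these.

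- **Harms question** (Study intervention/allocation to interventions): "Participants are also questioned at the end of the study regarding any adverse effects that took place during the study period". No other section describes a solicited question on harms.
- **Withdrawal** (same section): "Participants could also withdraw from the program at any given time". No exit contact is described.
- **Spontaneous route** (same section): "Participants are welcome to communicate with the research team if they have any questions/concerns during the program".
- **Yearly contacts**: the same section refers to "the adherence that will also be monitored by completing a questionnaire at the end of each year". Data collection tools has a second instrument, headed "Self-administered questionnaire – year 1, 2, and 3"; its listed contents include health and medication but not adverse effects.
- **Who is expected to stay** (Discussion): "participants who have successfully changed their lifestyle habits will be more inclined to remain actively involved", and to be reassessed.
- **Duration and risk** (Study design): a three-year programme with re-evaluation at one and two years, and no specific risk apart from those of taking up an active lifestyle.

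**The concern.** A single question at the end has two weaknesses. Recall is long: a minor injury in the first months would have to be remembered two or three years later. The question may also miss people who have left, and someone who stopped because of an injury is a natural candidate for leaving. The article itself predicts that those who stay will be a favourable subset.

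What is at stake is the harm count, including the active-lifestyle risks that Study design sets apart. Those risks are real here. The Health Challenge asks for 30 minutes of activity a day, and the example of a closing event includes soccer; by Table 1 the control option receives neither. If under-counting differed between options, a reader of counts by option could be misled.

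The article chooses the time point itself, so this is a stated choice and not a detail left to a fuller document.

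**Working it through.** The plan states no figure for harms, retention or coverage, so there is nothing to reproduce. The calculation below only gives a sense of scale.

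**Inputs from the article**
- Length T: 2 years (last stated re-evaluation) or 3 years (programme length).
- Existing contact: a questionnaire at the end of each year.

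**Assumptions (not in the article)**
- Share remaining at the end, R: 70%, 50% or 30%.
- Steady drop-out, meaning a constant rate of leaving, so the share still enrolled at time t is R^(t/T).
- The question reaches only those enrolled when it is asked, and leavers are not asked on exit.
- Recall is perfect, which favours the end question.

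**Formulas**
- On-study person-time per starter: T(1 − R)/(−ln R). This counts time actually spent on study. Using years started instead would credit each leaver with a full final year and understate coverage.
- End question: covers T·R, so its share is R(−ln R)/(1 − R). T cancels, so the share is the same for 2 and 3 years.
- Yearly question: with r = R^(1/T), it covers r + r² + … + r^T, so its share is r(−ln r)/(1 − r).

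**Numbers put in**
- End question, R = 0.7: 0.7 × 0.3567/0.3 = 0.832. R = 0.5: 0.5 × 0.6931/0.5 = 0.693. R = 0.3: 0.3 × 1.2040/0.7 = 0.516.
- Yearly, T = 2. R = 0.7, r = 0.8367: 0.8367 × 0.1783/0.1633 = 0.913. R = 0.5, r = 0.7071: 0.7071 × 0.3466/0.2929 = 0.837. R = 0.3, r = 0.5477: 0.5477 × 0.6020/0.4523 = 0.729.
- Yearly, T = 3. R = 0.7, r = 0.8879: 0.942. R = 0.5, r = 0.7937: 0.889. R = 0.3, r = 0.6694: 0.813.

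| Remaining at end | End question, 2 or 3 years | Yearly, 2 years | Yearly, 3 years |
|---|---|---|---|
| 70% | 83% | 91% | 94% |
| 50% | 69% | 84% | 89% |
| 30% | 52% | 73% | 81% |

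**Check with another drop-out pattern.** If leaving times are uniform and the drop-out share is d = 1 − R, the end question leaves (d/2)/(1 − d/2) uncovered and a yearly question leaves 0.5d/[T(1 − d/2)]. At d = 50% that is 33% uncovered, against 17% (2 years) or 11% (3 years). Coverage is therefore 67%, against 83% or 89%, close to the middle row of the table.

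The recall period falls from 24–36 months to about 12 months, whatever the drop-out rate.

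**The case against.** The strongest case on the other side is that this is a low-risk programme of menus, talks, coaching and voluntary challenges, described in a condensed article. Harms are neither a primary nor a secondary outcome. People can report concerns at any time. The analysis is to be by intention to treat, and the Discussion promises a specific analysis of selective drop-out. Exit procedures are often left to the full protocol.

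Much of this stands, and it rules out several stronger readings that a reader might infer.

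- **That everyone who leaves is never asked.** The text does not say so. It speaks of participants without limiting the question to completers, and withdrawal is from the programme. What can be said is that no provision for asking leavers is described.
- **That fewer than half will remain.** The Discussion's remark, "Adherence rates in WHPP are generally in the low range", concerns adherence in such programmes generally, not retention in this study. The article expects higher adherence in options A, B and C.
- **That a planned comparison of harms between options is invalid.** No such comparison is planned, and no drop-out by option is given, so a difference in bias between options is only possible.
- **That the article's statement on risk rests on this question.** It describes the known risks of taking part, excepts those of an active lifestyle, and is not drawn from collected data.

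The objection does not remove the main point. Spontaneous reporting is not systematic. The final questionnaire to all employees described in the Discussion concerns their view of the interventions and is not linked to harms. An analysis of drop-out cannot recover events that nobody asked about.

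**Conclusion.** The concern holds as a weakness in timing, not as an error or contradiction. One solicited question at the end, with two to three years of recall and no described provision for those who withdraw, is likely to under-count harms, because the article expects those who succeed to stay.

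In the illustration, a yearly question raises coverage of on-study person-time by about 8, 14 or 21 percentage points over two years, and 11, 20 or 30 over three, when 70%, 50% or 30% remain. These figures rest on assumed retention, steady drop-out and leavers not being asked. They show scale and do not predict the bias. Under-counting is likely but not proven. The change is worth making because it uses a contact that already exists.

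**What to change.** In Study intervention/allocation to interventions:

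1. Add the same adverse-effects question to the questionnaire completed at the end of each remaining year.
2. Ask it once when a participant withdraws.
3. Report counts by option, with the number of people asked on each occasion.

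**Cost.** A slightly longer online form and a minor ethics notification.

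**Limit.** Baseline ran from December 2016 to July 2018, and the article cites a registry update of March 2019. For the earliest baselines the one-year and two-year points fall around December 2017 and December 2018, so those contacts may already be past. For the latest they fall around July 2019 and July 2020. Missed contacts cannot be recovered, so ascertainment will differ by company start date, and the report should say so.
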